### Primary outcome measures

The main outcome measures are change in attentional bias, change in depressive symptomatology and mood response and recovery from stress.

#### Attentional bias

Change in attentional bias is assessed by means of the dot-probe task. In accordance with previous research [33], an attentional bias score is calculated for each participant, separately for pre- and post-assessment, by subtracting RTs on trials where the arrow replaces the positive picture (compatible trials) from trials where the arrow replaces the negative picture (incompatible trials). A positive score indicates an attentional bias towards positive pictures, whereas a negative score indicates a bias towards negative pictures.

#### Depressive symptoms

Changes in depressive symptoms are assessed with the IDS-SR self-report [52]. The IDS-SR contains 30 items that are rated on a 4-point scale (0 to 3). Possible total scores can thus range from 0 to 90 with higher scores indicating greater depression severity (i.e., 0–13 = *no depression*; 14–25 = *mild depression*; 26-38 = *moderate depression*; 39–48 = *severe depression*; > 48 = *very severe depression*. The IDS-SR is well validated and has been proven useful in detecting symptom change and residual symptoms in depressed patients [55].

#### Mood reactivity and recovery from stress

To investigate training effects on mood changes in response to a stressor, an adapted version of a speech task as used by Sanchez et al. [22] is used. At the beginning of this task, participants sit in front of a black computer screen and rest for a period of five minutes. Afterwards, they rate their mood, and are then informed by means of computer instructions, that they will get two minutes to prepare a five-minute-speech on the topic – e.g., “Why am I a good friend?”. This topic has effectively induced stress levels in patients with MDD in the study of Sanchez and colleagues. Participants are told that the speech will be video recorded and evaluated on its quality by two independent researchers. However, they are also informed that not everybody would have to give the speech eventually. Instead, the computer would randomly choose, who actually has to give the speech. During the following two-minutes of preparation, participants are allowed to take notes with pen and paper and, to increase the stress level, a clock on the computer-screen signals the time left. After preparation, participants again rate their current mood before the computer informs them, that they would not have to give the speech. They are then given another five minutes to rest and rate their mood for a last time afterwards. This procedure has successfully been used by Sanchez and colleagues to investigate the relation between attention bias and stress responses in depressed individuals.

Mood changes during the speech task are measured by means of a six-item, state version of the Spielberger State-Trait Anxiety Inventory (STAI; [56, 57]) and a state version of the international short form of the Positive and Negative Affect Schedule (I-PANAS-SF; [58]). The STAI-S contains six items related to anxiety (i.e., calm, tense, upset, relaxed, content, worried) that are rated on a 4-point scale (1 = *not at all* to 4 = *very much*). This short form of the STAI has been proven sensitive to fluctuations in state anxiety and shows comparable psychometric properties as the full-form [56]. The I PANAS-SF contains five items related to positive and five items related to negative affect, rated on a five-point scale (1 = *very slightly* or *not at all* to 5 = *extremely*) and has shown to be psychometrically acceptable [58].

### Secondary outcome measures

#### Trait anxiety

In line with earlier research on the effects of repeated Cognitive Bias Modification (CBM) sessions in depression [33], the 20-item Spielberger State-Trait Anxiety Inventory (STAI-T; [59]), is used to assess anxiety proneness. All items are rated on a Likert-scale ranging from 1 (*not at all*) to 4 (*very much*). The Dutch translation of the scale exhibits good psychometric properties [60, 61].

#### Positive and negative affect

To assess changes in general mood, the Positive and Negative Affect Schedule (PANAS; [62, 63] is used. The PANAS is a 20-item self-report measure consisting of two mood scales, one assessing positive and one assessing negative affect. Items are rated on a 5-point scale ranging from 1 (*very slightly or not at all*) to 5 (*extremely*). The Dutch translation of the PANAS has adequate psychometric properties [64].

#### Rumination

Ruminative thinking is assessed with the Ruminative Response Scale (RRS-NL), a subscale of the Response Styles Questionnaire (RSQ; [65]). This self-report scale contains 22 items assessing an individuals’ tendency to engage in rumination that is either self-focused (e.g., “think what am I doing to deserve this?”), symptom focused (e.g., “think about how hard it is to concentrate”) or focused on causes and consequences of having a depressed mood (e.g., “think I won’t be able to concentrate if I keep feeling this way”). Items are rated on a 4-point scale, ranging from 0 (*almost never*) to 4 (*almost always*). Next to a total rumination score, this questionnaire provides brooding and reflective pondering subscale scores, with brooding being considered the maladaptive component of rumination, which is associated with more depression [66]. The psychometric properties of the Dutch translation of the scale have been proven to be moderate to good [67].

#### Resilience

Resilience is assessed with the Resilience Scale (RS; [68]). This self-report questionnaire contains 25 items (e.g., “I feel that I can handle many things at a time.“), rated on the four-point scale (i.e., 1 = *strongly disagree* to 4 = *strongly agree*). The Dutch translation of the scale has been shown to be a reliable and valid instrument to measure the degree of individual resilience [69].

#### Cognitive transfer measures

To assess transfer to an attentional bias for verbal negative and positive information, the *emotional Stroop task* [70] is used. This task consists of three randomized blocks with valenced words (negative, neutral, and positive) that are presented in red, yellow, green, or blue on a computer screen. The words are selected from a database [71] and are matched for length and valence strength. Participants are instructed to indicate the ink color by naming the color of the word aloud, while ignoring the meaning of the words. The experimenter records reaction time (RT) and errors per block. A bias score is calculated by subtracting the RTs for the positive (negative) block from the reaction time for the neutral block. A positive score is indicative for an attentional bias for positive (negative) words.

The classical *Stroop color naming task* [72] is administered in order to (1) explore whether trait differences in cognitive control predict training effects on bias, and (2) to assess transfer effects of the training on cognitive control. As in the emotional Stroop task, participants have to name the color of words or crosses while ignoring their content. On neutral trials, rows of colored crosses are presented (e.g., “xxxx” printed in green). On congruent trials, color words are presented while the meaning of the word and its print color match (e.g., the word “green” printed in green). On incongruent trials, the meaning of the color words and its print color do not match (e.g., the word “green” printed in red). On these trials, participants thus have to inhibit their automatic response to read the word, resulting in slower RTs and more errors when naming the colors compared to on neutral trials. RTs to neutral (congruent) trials are subtracted from RTs to incongruent trials. Higher positive scores accordingly are indicative for less cognitive control.

In order to assess whether effects of the PT generalize to other forms of cognitive biases in depression, in this case the reduced ability to generate positive mental imagery of future events, the Prospective Imagery Task (PIT; [73, 74]) is used. Participants have to form mental images of ten positive and ten negative future scenarios (e.g., “You will have lots of energy and enthusiasm” or “You will feel misunderstood”) and to rate the vividness of each image on a 5-point scale ranging from 1 (*not imagine at all*) to 5 (*very vivid*). To obtain further information on the quality of the generated images, participants rate how much they feel as though they are actually experiencing the event while imagining it (1 = *not at all*; 5 = *completely*), how likely they think it is that the scenario happens to them in the future (1 = *not at all likely to occur*; 5 = *extremely likely to occur*) and how much they feel as though they are actually experiencing the event while imagining it (1 = *not at all*; 5 = *completely*). Although, for this study, we are primarily interested in positive mental imagery, we also include the negative items to allow for control of the general ability to generate prospective mental imagery. Internal consistency has been calculated for a Dutch sample by Blackwell and colleagues [75], where all subscales demonstrated good internal consistency (*α =* 0.83–0.90). At the end of the task, participants are asked to estimate how often they had retrieved a memory from a past event in order to vividly imagine the described scenario (i.e., 0–100 % of the cases). To control for everyday use of mental imagery when analyzing effects on positive imagery ability, the Spontaneous Use of Imagery Scale (SUIS) [76] is administered. The scale consists of 12 items, such as “If I am looking for new furniture in a store, I always visualize what the furniture would look like in particular places in my home”, that are rated on a 5-point scale (1 = *never appropriate*; 5 = *always appropriate*). The SUIS has good psychometric properties and Blackwell et al. [75] report good internal consistency in a Dutch sample (*α* = 0.81).

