### Analysis plan

#### Clinical evaluation

In accordance with the Consolidated Standards of Reporting Trials (CONSORT; [84]), all analyses of the primary and secondary outcome parameters will be carried out in accordance with the intention-to-treat (ITT) principle. Missing values due to drop-out will be imputed (e.g., by using multiple imputation (MI) or expectation maximization (EM)). Additional sensitivity analyses will be conducted to gauge the robustness of the findings, by including and excluding these participants in the analysis.

ABM effects on the primary outcome measures, attentional bias and depressive symptoms, will be tested by means of RM ANOVAs, with condition (PT, ST) as between-subjects factor and time (pre-test, post-test) as within-subjects factor. Likewise, training effects on stress responses will be investigated with a 2 (condition: PT, ST) × 3 (time: before stress, anticipatory stress, stress recovery) RM ANOVA with I PANAS-SF and STAI-S scores as dependent variables. All analyses will be conducted with and without covariates, in case variables are unevenly distributed across groups (e.g., bias or depression at baseline, number of previous depressive episodes, or number of completed training sessions), to test the robustness of the results. To investigate long-term effects of ABM on depressive symptoms, the analysis of this primary outcome parameter will be repeated over five time points (baseline, post-test, one, six, and 12 months follow-up).

Effects on secondary outcome measures will be analyzed by means of ANOVAs or ANCOVAs over two time points (baseline, post-test) in case of the cognitive transfer measures, and over four time points (baseline, post-test, one and six months follow-up), in case of rumination, positive and negative affect, and resilience.

Exploratory analyses will be directed at the process measures and will additionally be performed to take the role of potential moderators into account, such as timing of the training (i.e., during waiting period vs. next to UC) type of UC (IPT, CBT, psychiatric care), or to predict training effects based on other disorder-related characteristics assessed during baseline.

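### The emotional Stroop bias score has the opposite sign to its stated interpretation, so a fall in negative verbal bias would read as a rise

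*Protocol article*

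**What the plan says.** All the relevant text is in the protocol article, Secondary outcome measures, Cognitive transfer measures.

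- **Task.** "Participants are instructed to indicate the ink color by naming the color of the word aloud, while ignoring the meaning of the words". Negative, neutral and positive words come in separate blocks, and reaction time and errors are recorded per block.
- **Formula.** "A bias score is calculated by subtracting the RTs for the positive (negative) block from the reaction time for the neutral block".
- **Interpretation.** "A positive score is indicative for an attentional bias for positive (negative) words".

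The next paragraph describes the classical Stroop task and links it to the emotional one: "As in the emotional Stroop task, participants have to name the color of words or crosses while ignoring their content". Trials on which the reading response must be inhibited are described as "resulting in slower RTs and more errors when naming the colors compared to on neutral trials", and the score is built accordingly: "RTs to neutral (congruent) trials are subtracted from RTs to incongruent trials". A higher positive value there means less cognitive control.

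Under Clinical evaluation, the cognitive transfer measures are to be analysed by ANOVA or ANCOVA over baseline and post-test.

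**The concern.** In a colour-naming task the word's meaning is the distractor. A patient whose attention is caught by negative words should take longer to name colours in the negative block than in the neutral block. Neutral minus negative is then below zero. The protocol nevertheless treats a score above zero as the sign of a bias. Taken literally, a patient who is faster on negative words than on neutral ones would be classed as biased towards them.

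At stake is the direction of every conclusion on this measure. Table 1 lists it as the only test of whether training on pictures carries over to verbal attentional bias, and that transfer is one of the study's stated questions. If the definition is applied as written, a beneficial effect would be reported as harm, and a harmful one as benefit.

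**Working it through.** No planned figure has to be reproduced. The check concerns the sign of a definition.

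**Inputs from the protocol**

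- Protocol score: S = RT(neutral block) − RT(emotional block), calculated separately for positive and negative words.
- Stated rule: S > 0 means a bias for words of that valence.
- Word meaning is to be ignored in both Stroop tasks. In the classical task, content that has to be inhibited slows the response.

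**Algebra**

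Let I be the slowing caused by attention to word meaning, so that RT(emotional) = RT(neutral) + I. Then:

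- Protocol score: S = RT(neutral) − [RT(neutral) + I] = −I.
- Reversed score: S′ = [RT(neutral) + I] − RT(neutral) = +I.

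A bias means I > 0, which gives S < 0. This holds whatever the reaction times are.

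**Numerical illustration**

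The protocol gives no Stroop times, so these are assumptions: a neutral RT of 700 ms and four pre-to-post reductions in interference from negative words.

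| I, pre → post (ms) | Protocol score, pre → post | Change | Reversed score, pre → post | Change |
|---|---|---|---|---|
| 20 → 5 | −20 → −5 | +15 | 20 → 5 | −15 |
| 40 → 20 | −40 → −20 | +20 | 40 → 20 | −20 |
| 60 → 10 | −60 → −10 | +50 | 60 → 10 | −50 |
| 40 → −10 | −40 → +10 | +50 | 40 → −10 | −50 |

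For the second row: 700 − 740 = −40 before and 700 − 720 = −20 after, a change of +20. In every row interference falls and the protocol's score rises. The last row is the plainest. The score passes from negative to positive, so the stated rule declares a negative bias just when the slowing has gone.

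**Comparison with the other reaction-time scores**

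- *Classical Stroop:* incongruent minus neutral (or congruent). Interference makes it positive, and positive is read as less control. Consistent.
- *Dot-probe (Attentional bias section):* RT when the arrow replaces the negative picture minus RT when it replaces the positive picture. Attention already on the positive picture speeds the response there and makes the score positive, which matches "A positive score indicates an attentional bias towards positive pictures, whereas a negative score indicates a bias towards negative pictures". Consistent.
- *Emotional Stroop:* neutral minus emotional. Interference makes it negative, but positive is read as bias. Inconsistent.

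**Effect on the planned test**

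The error multiplies the outcome by −1. Sums of squares do not change, so F, the two-sided p-value and the absolute effect size for condition by time stay the same. Only the sign of the estimate, and so the reading of it, is reversed.

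**The case against.** The strongest reply is that this is a slip of wording with little consequence. It is easy to invert a subtraction in prose, the following sentence shows what was meant, and the authors got the order right for the other two scores. The measure is secondary, and the Discussion places transfer to verbal material among exploratory questions. It plays no part in the sample size, the mediation analyses or the economic evaluation. Block times are recorded, so the direction can always be recovered. Nor do the documents show that analysts would follow the sentence literally. All of this stands. It limits how serious the point is, but the definition as written is still wrong.

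A second reply is that the protocol states the link between interference and slowing only for the classical task, where a colour word conflicts with the ink colour. Emotional words carry no such conflict, and the two scores measure different things, so they need not share a sign. It is true that the protocol never states the expected direction for the emotional task. The inference rests on the shared instruction to ignore content, which the protocol itself draws attention to. The difference in sign between the two Stroop scores supports the point but is not itself the error. The error is the mismatch within the emotional score, and the protocol offers no reason why attention to a word's meaning should speed up naming its colour.

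A third reply is that the protocol gives no meaning to a negative score, so reading a move from −40 to −20 as more bias is an extrapolation. That is fair for rows that stay below zero. It does not help where the score crosses zero, or where a patient with marked interference fails the stated criterion for bias.

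**Conclusion.** The concern holds. The emotional Stroop formula and its stated interpretation contradict each other, and nothing elsewhere in the protocol article corrects this. Applied as written, the score is exactly −1 times the interference it is meant to represent, for positive and negative words alike, so every directional conclusion on verbal attentional bias would be reversed.

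This rests on one premise: that attention to word meaning slows colour naming. The premise follows from the task instruction and from the protocol's own account of the classical Stroop. The millisecond values are illustrative and the conclusion does not depend on them.

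The error has clear limits. It affects one secondary outcome. The primary dot-probe score has the right sign, and test statistics, two-sided p-values and absolute effect sizes are unaffected. It should be corrected before analysis, but it does not threaten the main results. Whether the analysis would actually carry the error through cannot be told from the document.

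**What to change.** Define the score as reaction time in the positive (or negative) block minus reaction time in the neutral block, and keep the statement that a positive score indicates a bias for words of that valence. This also makes slowing positive in both Stroop scores. Alternatively, keep the present subtraction and state that a negative score indicates bias. Change only one of the two, since changing both would restore the conflict.

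Check that the scoring code follows the corrected definition before the data are analysed, and state in the report which direction means bias.

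The cost is one sentence and a check of the code. Data collection, sample size and the planned tests do not change.

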#### Process measures

Training task performance is assessed for both the PT group and the ST group by comparing average RTs for incompatible trials (in the PT: catch trials) to average RTs for compatible trials across training blocks and sessions. Based on this, learning curves within each session and losses of training effects between sessions will be investigated. To evaluate effects of the online training sessions on mood, three visual analogues scales (VAS) are administered prior to and following each dot-probe session. The VAS scales were adopted from Sanchez et al. [22] and consist of three items each: happy mood (happy, optimistic, joyful), anxious mood (nervous, tense, anxious), and sad mood (depressed, upset, sad). Participants are asked to indicate their current mood on a line with anchor points ranging from 0 (*not at all*) to 10 (*very much*).

To control for possible placebo effects of the intervention, the Credibility/Expectancy Questionnaire (CEQ; [77]) is used. The CEQ is a short self-report questionnaire that measures how credible and convincing the patient experiences the intervention and what the patient expects from it. The questionnaire in this study has been adapted from a Dutch version of this questionnaire for chronic back pain patients [78]. It comprises three questions regarding the credibility of the intervention and three questions assessing participants expectations, all of which are answered on a 9-point scale (1 = *not at all* to 9 = *very much*).

#### Cost-effectiveness

The Trimbos/iMTA questionnaire for Cost associated with Psychiatric Illness (TiC-P; [79]) is used to measure direct medical, direct non-medical and indirect non-medical costs resulting from health care uptake and productivity losses associated with MDD. The TiC-P is the most widely used health service receipt interview for economic evaluations in the Netherlands. The EuroQol (EQ-5D-3 L) is administered to measure health related quality of life [80]. It is a frequently used, preference-based, generic index instrument for the calculation of health-related quality of life in terms of quality adjusted life years (QALYs; [81]).

### Procedure

Eligible patients who agreed to participate, receive a printed version of the TiC-P and are asked to fill it in at home and bring it to the baseline session (session 1). At start of this session, participants again receive written and oral information about the study. Then, they provide written informed consent and hand in the filled-in TiC-P. In a computer room, first of all, a range of disorder-related characteristics are assessed by the experimenter, including the age of onset of the depression, the number of depressive episodes during life time, the amount of psychological treatment for previous episodes, as well as information about the current episode (i.e., duration, number of psychological treatment sessions, and duration and dosage of pharmacological treatment). Afterwards, participants are seated in front of a computer, where they complete the dot-probe task (pre-assessment), which is preceded by a brief assessment of mood state (VAS). Next, they fill in computerized versions of all questionnaires (i.e., IDS-SR, STAI-T, RRS, RS, PANAS, SUIS, EQ-5D-3 L), before they complete the Stroop tasks. Finally, the PIT is administered and an appointment is made for the first training session, which again takes place at Pro Persona, within 5 days after the baseline session. Although the training is offered as web-based intervention, participants complete the very first training session under supervision of a researcher, to ensure that task instructions are well-enough understood and that the task can be completed correctly at home. The importance of completing the training by themselves, in a calm, distraction-free environment (i.e., without any music, television etc. on the background) is emphasized, both verbally and in the written task instructions. This is of particular relevance, as previous research suggests that when working memory load is high, which is likely the case in a home-environment with task-irrelevant distractions, ABM may be less or not effective [82].

During the first training session (session 2), participants receive written and verbal practical information regarding the online training-program. They then complete the first training which is, like all dot-probe trainings, flanked by brief mood state measures (VAS). Afterwards, the CEQ is administered and appointments are made for the seven training sessions (session 3–9), as well as for the post-assessment (session 10). The eight training sessions are distributed across two weeks, with four weekly sessions. During the two weeks of training, participants receive automated e-mails reminding them of the planned sessions. In case, participants do not complete the planned sessions, even though they have been reminded by e-mails, they are given a call by the experimenter who asks them to still complete the session. The post-assessment, which again takes place at Pro Persona, is scheduled at least one week and a maximum of two weeks after the last training session. The post-assessment is comparable to the baseline assessment but without the Tic-P and the RS, and with the additional speech task. Afterwards, appointments are made for the subsequent follow-up assessments and participants receive a reimbursement for their travel cost (15 Euros).

During the first two follow-up assessments (session 11 & 12), participants complete questionnaires via the internet (IDS-SR, STAI-T, RRS, RS, PANAS, EQ-5D-3 L). At 12 months follow-up (session 13), the MINI is administered via telephone to assess the diagnostic status of depression. Moreover, participants complete the IDS-SR, EQ-5D and Tic-P via internet. After having filled in the questionnaires, participants receive a debriefing form with contact information of the coordinating investigator, who can be contacted in case of questions. The use of medication as well as the number of psychological treatment sessions is monitored at the post-test and all follow-up measures. For an overview of all measures and corresponding time points, see Table 1.

**Table 1 Tab1:** Overview of all measures and corresponding time points

Domain	Target Concept (Measure)	T0	T1	Training 1	Training 2–8	T2	T3	T4	T5
Screening measures	Inclusion Criteria Interview	•							
	Diagnostic status (MINI)	•							•
Primary outcome measures	Attentional Bias (Dot-probe)		•			•			
	Depressive Symptomatology (IDS-SR)		•			•	•	•	•
	Mood response and recovery from speech task (I PANAS-SF & short STAI-S)					•			
Secondary outcome measures	Trait Anxiety (STAI-T)		•			•	•	•	
	Positive and Negative Affect (PANAS)		•			•	•	•	
	Rumination (RRS)		•			•	•	•	
	Resilience (RS)		•				•	•	
	Cognitive transfer -Verbal attentional bias (emotional Stroop task) -Attentional control (classical Stroop task) -Mental imagery (PIT, SUIS)		•			•			
Process measures	Attentional Bias (Dot-probe training trials)			•	•				
	Mood in response to training (VAS)			•	•				
	Credibility and Expectancy (CEQ)			•					
Cost-effectiveness	Quality of Life (EQ-5D-3 L)		•			•	•	•	•
	Costs (TIC-P)		•						•

*Note*. T0 = Intake; T1 = Baseline; T2 = Post-assessment; T3 = One month follow-up; T4 =Six months follow-up; T5 = 12 months follow-up; Measures at T1, Training 1 and T2 are administered by an experimenter, who is blinded to the training conditions. Training 2–8 and all follow-up measures (T3–T5) are administered via the internet

